### Statistical analysis plan

Analysis of efficacy will be on the basis of intention-to-treat. Gametocyte densities will be compared between treatment groups using one-way analysis of variance on log-transformed gametocyte densities; gametocyte carriage during follow-up will be estimated by calculating for each arm the area under the curve (AUC) of both the gametocyte density and gametocyte prevalence against time. The AUC between treatment groups will be compared using non-parametric tests. The Kaplan-Meier estimator will be used to compare gametocyte clearance times between study arms for individuals who are gametocyte positive by QT-NASBA at enrolment.

For the non-inferiority comparison between the PQ arms, the 95% confidence around the gametocyte prevalence in the PQ 0.4/0.2 mg/kg arms at day 7 will be compared to the non-inferiority limit determined by the prevalence in the PQ 0.75 mg/kg arm and delta.

For the DMFA, the proportion of infectious individuals will be compared between arms using chi-squared statistics. The proportion of infected mosquitoes will be compared between groups using mixed models to account for clustering within cages fed on blood from the same individual.

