### Treatment and follow-up

All participants in the trial will receive a complete 3-day course of DHA-PPQ based on body weight according to the manufacturer’s instructions. DHA-PPQ is available as both paediatric (dihydroartemisinin 20 mg/piperaquine 160 mg) and adult (dihydroartemisinin 40 mg/piperaquine 320 mg) formulations. Participants in the three intervention arms are randomized to receive a single 0.75 mg/kg, 0.40 mg/kg or 0.20 mg/kg dose of PQ base on day 2 with the third dose of DHA-PPQ. Each tablet of PQ contains 15 mg base and, to ensure the accuracy of doses <15 mg, the tablet will be reconstituted in 15 ml water to achieve a 1 mg/ml concentration and the required dose dispensed using a sterile syringe. A nurse directly observes all treatments and treatment may be repeated once if a participant vomits any of the drugs within 30 minutes of being administered.

Each participant attends eight scheduled follow-up visits on days 3, 7, 10, 14, 21, 28, 35, and 42 for clinical evaluation and blood sampling. Blood samples from a finger prick are collected for gametocyte (QT-NASBA) and asexual parasite clearance (microscopy and polymerase chain reaction) and haemoglobin measurement. Additional tests may be requested during unscheduled visits to the clinic (Table 1). Thick blood films stained with 10% Giemsa for 10 minutes are examined under 1000-fold magnification by trained microscopists. Asexual parasite density is determined by counting the number of asexual parasites per white blood cell (WBC) until 500 WBCs have been counted (assuming a mean WBC count of 8,000/μl) and results presented as parasites/μl.

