### Sample size considerations

The sample size was calculated to detect a difference in gametocyte prevalence on day 7 after treatment, between the control (DHA-PPQ only) and 0.75 mg/kg PQ arm, and between this and lower doses of PQ (0.4 mg/kg and 0.2 mg/kg). Two hypotheses underscore the sample size calculation: 1) treatment with PQ (any dose) and DHA-PPQ results in significantly lower gametocyte carriage compared to treatment with DHA-PPQ alone; and 2) a single dose of 0.4 mg base/kg or 0.2 mg base/kg PQ administered with the last dose of DHA-PPQ has similar gametocytocidal efficacy as a single 0.75 mg base/kg dose.

For the first hypothesis, the underlying assumption is that, although a substantial proportion of asymptomatic carriers also carry gametocytes [20], treatment with an ACT alone would reduce gametocyte prevalence on day 7 to around 18%, and the addition of PQ at 0.75 mg/kg will further reduce the prevalence by 50% (that is, to 9%). A sample size of 300 participants per arm would have 90% power to detect this difference, at the 5% significance level, allowing for 10% of enrolees being non-compliant or lost to follow-up.

In the second hypothesis, assuming a prevalence of 9% in the standard PQ arm, 300 participants would be sufficient, with 90% power, to detect a confidence interval around the prevalence in the lower dose PQ arm below 16% and 80% power to detect that this confidence interval is entirely below 15%.

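### Intention-to-treat is the only set named for the non-inferiority comparison of primaquine doses; missed day-2 doses bias it modestly towards non-inferiority

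*Protocol article*

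**What the plan says.** The Statistical analysis plan section of the protocol article opens with "Analysis of efficacy will be on the basis of intention-to-treat". It then describes the non-inferiority comparison: the 95% confidence interval for day-7 prevalence in each lower-dose arm "will be compared to the non-inferiority limit determined by the prevalence in the PQ 0.75 mg/kg arm and delta". No other analysis set is named anywhere in the article.

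The Sample size considerations section gives two hypotheses. The first is superiority of primaquine over DHA-PPQ alone. The second is that a lower dose "has similar gametocytocidal efficacy as a single 0.75 mg base/kg dose". On the planning values, the section supposes that "treatment with an ACT alone would reduce gametocyte prevalence on day 7 to around 18" (per cent), and the second hypothesis is sized "assuming a prevalence of 9% in the standard PQ arm". The 300 per arm is said to give 90% power "to detect a confidence interval around the prevalence in the lower dose PQ arm below 16" (per cent), and 80% power for a limit of 15%. Under the first hypothesis the number is described as "allowing for 10% of enrolees being non-compliant or lost to follow-up".

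The Treatment and follow-up section gives primaquine once, a "dose of PQ base on day 2 with the third dose of DHA-PPQ". It also states that a nurse observes all treatments directly and that a vomited dose may be repeated once.

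**The concern.** One analysis population serves two hypotheses that respond to missed treatment in opposite ways. For superiority over control, keeping participants who did not take primaquine dilutes the effect, which is conservative. For non-inferiority between two primaquine arms, the same dilution makes the arms look alike.

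The design leaves room for this. Primaquine is a single dose given two days after enrolment, so a randomised participant can miss it entirely. Whatever the assigned dose, that participant has then had DHA-PPQ alone. Because the limit is tied to the 0.75 mg/kg arm, it rises with dilution in that arm and gives no protection. The trial seeks the lowest effective dose, so the error at stake is declaring a weaker dose non-inferior.

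**Working it through.** **Inputs** (Sample size considerations unless noted)
- Day-7 prevalence without primaquine: 18%.
- Day-7 prevalence with 0.75 mg/kg: 9%.
- Implied margin: 16% − 9% = 7 points (90% power) or 15% − 9% = 6 points (80% power).
- 300 per arm, or 300 × 0.9 = 270 if a full 10% is not evaluable.
- Limit: prevalence in the 0.75 mg/kg arm plus delta (Statistical analysis plan).

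**Reproducing the plan's figures.** For a two-arm comparison with 9% in both arms, SE = √(2 × 0.09 × 0.91 / n) and power = Φ(margin/SE − z).
- n = 270: SE = 0.02463. At one-sided 5%, power is 88.4% (7 points) and 78.6% (6 points).
- n = 300: SE = 0.02337. At one-sided 5%, power is 91.2% and 82.2%.

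Both are close to the stated 90% and 80%, so margins of 6 to 7 points are a reasonable reading.

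**Dilution.** Let a fraction c miss primaquine in each of the two arms and carry 18%. Let the true difference among those who take it equal the margin m.
- 0.75 mg/kg arm: 0.09(1 − c) + 0.18c
- Lower-dose arm: (0.09 + m)(1 − c) + 0.18c
- Difference: m(1 − c)

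At c = 10% the arms become 9.9% and 16.2% for m = 7 points (difference 6.3), or 9.9% and 15.3% for m = 6 points (difference 5.4).

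**Error rate.** This is the chance that the upper 95% limit of the difference falls below m when the lower dose truly sits at the margin. Normal approximation for c = 10%, m = 7 points, n = 300:
- SE = √(0.099 × 0.901/300 + 0.162 × 0.838/300) = 0.02738
- Φ((0.070 − 0.063)/0.02738 − 1.96) = Φ(−1.704) = 4.4%

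Full binomial enumeration with the Newcombe interval, 270 to 300 per arm:

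| Missed primaquine | 6-point margin | 7-point margin |
|---|---|---|
| 0% | 2.5% | 2.5% |
| 2% | 2.8% | 2.8% |
| 5% | 3.2–3.3% | 3.3% |
| 10% | 4.1% | 4.3–4.4% |

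**Sensitivity to how the rule is read**
- Literal rule: a one-arm 95% Wald interval set against the observed 0.75 mg/kg prevalence plus delta, 300 per arm. Error is already 7.4–7.6% with no missed doses and becomes 11.4–11.7% at c = 10%. The direction is the same.
- Limit fixed at 15% or 16%: missed doses work against non-inferiority. With a one-arm Wald interval and 300 per arm, error falls from 4.1% to 3.0% at the 15% limit and from 3.2% to 2.6% at the 16% limit. The bias therefore depends on the limit moving with the 0.75 mg/kg arm, which is how the Statistical analysis plan section words it.

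**The case against.** The strongest reply is that this is an omission. A condensed article may leave supportive analysis sets to the full protocol or SAP, neither of which is shown, and the article does not say that intention-to-treat excludes other sets. That holds in part: a per-protocol set may exist elsewhere. But the article does fix the population for efficacy, and for the non-inferiority claim that choice errs in the anti-conservative direction. Questioning a stated choice is different from reporting a gap.

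The second reply is size, and it stands. Dosing is one nurse-observed dose, with a repeat permitted after early vomiting. At 2% missed, error is 2.8% against 2.5%, which is of little consequence.

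The third reply is that a per-protocol set is chosen after randomisation. It restores 2.5% only if exclusion is unrelated to outcome. This also stands, and it is why the per-protocol set should accompany intention-to-treat and not replace it.

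A reader might infer three stronger points that the article does not support:
- *That the plan expects 10% non-compliance.* The 10% is a sample size allowance, stated under the first hypothesis, that pools non-compliance with loss to follow-up. People lost before day 7 have no outcome, so they raise a missing-data question and not this dilution.
- *That the sample size section removes non-compliers and so contradicts intention-to-treat.* The section does not say how the allowance was applied. At one-sided 5% with unpooled variance, the first hypothesis needs 242.6 per arm. Dividing by 0.9² = 0.81, the usual inflation when non-compliers are kept, gives 299.6. Removal, dividing by 0.9, gives about 270, or 297 if a continuity correction is first applied (267/0.9). Either could lie behind 300, and both need a one-sided test that the text does not state.
- *That dosing is loosely controlled.* Direct observation of every treatment points the other way.

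**Conclusion.** The point holds as a modest weakness in a stated choice. With the limit tied to the 0.75 mg/kg arm, an intention-to-treat comparison alone is biased towards non-inferiority whenever participants miss primaquine. The inflation in one-sided error is about 0.3 percentage points at 2% missed and 0.7 to 0.8 at 5%. It is 1.6 to 1.9 in the extreme case where the whole pooled 10% allowance is missed primaquine with a day-7 result. The low end is the most plausible.

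These figures assume that non-takers have the control prevalence, that missing is equal in the two arms, and that the analysis uses an interval for the difference with a margin of 6 to 7 points. The direction would reverse if the limit were a fixed 15% or 16%. The superiority comparison is unaffected, because there intention-to-treat is the conservative choice.

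**What to change.** Keep intention-to-treat for the comparison with DHA-PPQ alone. For the two non-inferiority comparisons, also analyse a per-protocol set, defined before the data are analysed: participants recorded as having taken their assigned treatment under the plan's own dosing rules, with a day-7 QT-NASBA result. Claim non-inferiority only if the upper confidence limit meets delta in both sets. Report how many participants in each arm missed primaquine, separately from those lost before day 7, so that readers can judge the dilution.

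The cost is a second run of the same analysis. Treatment is directly observed and day-7 QT-NASBA is already scheduled, so no new data collection should be needed. Some power is lost. In the extreme case of 270 instead of 300 per arm, at one-sided 2.5% and with equal prevalence of 9%, power for the per-protocol comparison falls from 85.0% to 81.1% (7 points) or from 72.8% to 68.3% (6 points). With few missed doses the loss is much smaller. The per-protocol set also brings possible post-randomisation selection. Requiring agreement limits that risk but does not remove it.

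### The non-inferiority rule ignores sampling error in the 0.75 mg/kg arm, so a dose at the margin passes about 5% of the time rather than the implied 2.5%

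*Protocol article*

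**What the plan says.** The Statistical analysis plan section of the protocol article states the decision rule in one sentence. The interval is "the 95% confidence around the gametocyte prevalence in the PQ 0.4/0.2 mg/kg arms at day 7", that is, an interval for one arm's prevalence. It "will be compared to the non-inferiority limit determined by the prevalence in the PQ 0.75 mg/kg arm and delta". The section mentions no interval for the difference between arms and no allowance for uncertainty in the 0.75 mg/kg prevalence.

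Sample size considerations uses the same one-arm construction. It begins "assuming a prevalence of 9% in the standard PQ arm, 300 participants would be sufficient, with 90% power", and the aim is "to detect a confidence interval around the prevalence in the lower dose PQ arm below 16" per cent. The full pair of targets is 90% power for a limit of 16% and 80% power for a limit of 15%: "below 16% and 80% power to detect that this confidence interval is entirely below 15" per cent. Delta is never given as a number. Against 9%, the two limits imply 16 − 9 = 7 points and 15 − 9 = 6 points.

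Randomisation and blinding gives 1:1:1:1 allocation, so the reference arm is planned to be the same size as each lower-dose arm.

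**The concern.** Non-inferiority is a statement about a difference between two prevalences, and both are estimated. If only the lower-dose arm's error enters the interval, the comparison uses too small a standard error and is too easy to pass. The fault favours declaring a weaker dose adequate.

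Day-7 gametocyte prevalence is the primary endpoint. Similarity of the lower doses to 0.75 mg/kg is one of the two hypotheses that size the trial, and the Discussion presents the minimal gametocytocidal dose as the central question. The rule is applied to two doses, so there are two chances of a false claim.

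**Working it through.** **Inputs.** Reference prevalence 9%, 300 per arm and a 10% allowance for loss (270 evaluable) come from Sample size considerations. The margin of 6 or 7 points is inferred from the 15% and 16% limits. The 95% level comes from the Statistical analysis plan section; an upper limit at that level implies a one-sided error of 2.5%.

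**Rule as stated.** Declare non-inferiority if U(p̂L) < p̂R + δ, where U is the upper 95% limit for the lower-dose arm alone and p̂R is the observed 0.75 mg/kg prevalence.

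**1. The plan's own power.** Both arms at 9%, all pairs of binomial outcomes enumerated:

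| Method | n per arm | δ = 7 points (stated 90%) | δ = 6 points (stated 80%) |
|---|---|---|---|
| Stated rule, Wilson | 300 | 90.0% | 81.2% |
| Stated rule, Clopper-Pearson | 300 | 89.7% | 80.7% |
| Stated rule, Wald | 300 | 93.1% | 86.2% |
| Stated rule, Wilson | 270 | 87.1% | 77.3% |
| 95% Newcombe interval for the difference | 300 | 84.0% | 71.4% |
| 95% Newcombe interval for the difference | 270 | 80.0% | 67.2% |

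The literal rule with Wilson or Clopper-Pearson limits reproduces the stated pair at 300 per arm. A 95% interval for the difference does not.

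**2. How much too narrow.** With v = p(1 − p)/n and equal n, the ratio of the interval used to the interval needed is √[vL/(vL + vR)].

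- Lower dose 15%: 0.15 × 0.85 = 0.1275; reference 0.09 × 0.91 = 0.0819. √(0.1275/0.2094) = 0.780, so 22% too narrow.
- Lower dose 16%: 0.16 × 0.84 = 0.1344. √(0.1344/0.2163) = 0.788, so 21% too narrow.
- Equal prevalences: √(1/2) = 0.707, so 29% too narrow.

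At the margin the reference arm's standard error is about 0.8 of the test arm's: √(0.0819/0.1275) = 0.80 and √(0.0819/0.1344) = 0.78.

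**3. False non-inferiority, approximate.** When the true difference equals δ, the probability of passing is Φ(−1.96 × √[vL/(vL + vR)]).

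- δ = 6: Φ(−1.96 × 0.780) = Φ(−1.53) = 6.3%.
- δ = 7: Φ(−1.96 × 0.788) = Φ(−1.55) = 6.1%.

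**4. False non-inferiority, exact enumeration.** Reference 9%, lower dose at 15% or 16%, n = 270 to 300:

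| Interval | δ = 6 | δ = 7 |
|---|---|---|
| One-arm Wilson | 5.4-5.5% | 5.4% |
| One-arm Clopper-Pearson | 5.2-5.3% | 5.1% |
| One-arm Wald | 7.6-7.8% | 7.4-7.5% |
| Newcombe, difference | 2.5% | 2.5% |

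**5. Two doses.** If both lower doses lie at the margin (n = 300, shared reference arm), the chance of at least one false claim is about 9-10% with Wilson or Clopper-Pearson and 13-14% with Wald. Under the Newcombe rule it is about 4.7%.

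**6. Sensitivity to the reference prevalence.** For δ of 5 to 7 points, the one-arm rule's error across the three interval methods is about 3.5-7.2% if the true reference is 3%, 4.1-7.6% at 5% and 5.6-8.2% at 12%. With Wilson or Clopper-Pearson at 3-5% it is about 3.5-4.7%, still above 2.5%.

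**The case against.** **The limit may be fixed, not observed.** The article does not use the word observed, and the sample size section writes the limits as 15% and 16%. With a fixed limit and a true reference of exactly 9%, the Wilson or Clopper-Pearson error is 1.7-2.7% (3.2-4.1% with Wald). This reading does not rescue the rule. The analysis sentence ties the limit to the 0.75 mg/kg arm's prevalence, and the fixed limit does not reproduce the stated power pair. If the true reference were 7%, the error would be 11-22%. What stands is that "observed" is an interpretation, though the natural one.

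**The 2.5% target is inferred.** The only stated significance level, 5%, belongs to the first hypothesis. A conventional two-sample comparison at one-sided 5% with 270 evaluable gives 88.4% and 78.6% power, also close to the stated figures, so the power match does not prove what was intended. But that comparison corresponds to a 90% interval, and the article specifies 95%. If a one-sided 95% bound on the single arm was meant, the error is about 8-12% against 5%, so the inflation remains.

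**Stronger readings.** A reader might infer an error near 8%, three times nominal. That needs a Wald interval, which the article never names and whose power at 300 per arm does not match the stated figures; part of the excess is Wald's own poor coverage. A reader might also take the interval to be a third too narrow, or the reference arm's error to be as large as the test arm's. At the margin neither is true, and 29% is reached only at equal prevalences. Nor is the whole two-dose figure due to this fault, since the corrected rule also exceeds 2.5% across two doses.

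**The article condenses a fuller plan.** This would excuse missing detail, such as the interval method. It does not excuse a decision rule that is stated and is wrong as stated.

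**Conclusion.** The point holds: the rule is wrong as written. It omits the sampling error of a randomised reference arm of equal size and so roughly doubles the false non-inferiority rate per dose, to 5.1-5.5% against an implied 2.5% with the interval methods that match the stated power. Up to 7.4-7.8% is possible if Wald limits are used. The direction is secure. The size rests on four assumptions: the limit uses the observed 0.75 mg/kg prevalence, the 95% interval is two-sided, delta is 6 or 7 points, and the true reference prevalence is near 9%.

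**What to change.** Replace the rule with: for 0.4 mg/kg and 0.2 mg/kg separately, compute the two-sided 95% confidence interval (Newcombe or Miettinen-Nurminen) for the difference in day-7 gametocyte prevalence, lower dose minus 0.75 mg/kg, and declare non-inferiority only if its upper limit is below delta. State delta as a number.

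This changes one sentence and needs no new data. Its cost is power, which should be restated in Sample size considerations: about 84% (7 points) or 71% (6 points) at 300 per arm, and about 80% or 67% at 270 evaluable.

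For scale, keeping the stated power would need n = (zα + zβ)² × 2 × 0.0819/δ² evaluable per arm. For 7 points and 90% power this is (1.96 + 1.282)² × 0.1638/0.0049, or 352. For 6 points and 80% power it is (1.96 + 0.842)² × 0.1638/0.0036, or 358. Dividing by 0.9 for loss gives 392 and 398, against 300 planned. If enrolment cannot change, the lower power should simply be reported.

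### The non-inferiority rule ignores sampling error in the 0.75 mg/kg arm and does not require a lower dose to beat DHA-PPQ alone before it is called similar

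*Protocol article*

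**What the plan says.** The Statistical analysis plan section of the protocol article takes the 95% interval around day-7 gametocyte prevalence in each lower-dose arm. It compares that interval with a "non-inferiority limit determined by the prevalence in the PQ 0.75 mg/kg arm and delta". No number is attached to delta there.

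The Sample size considerations section supplies the figures. For control, "treatment with an ACT alone would reduce gametocyte prevalence on day 7 to around 18"%. For the reference dose, prevalence is assumed to halve, to 9%. For the lower doses it gives two limits. One is 16%, with a stated power of 90%. The second is put as "80% power to detect that this confidence interval is entirely below 15"%. Against 9%, these imply a delta of 7 or 6 points.

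The same section states as its first hypothesis that "treatment with PQ (any dose) and DHA-PPQ results in significantly lower gametocyte carriage compared to treatment with DHA-PPQ alone". Neither section says that a lower dose must meet this before it is called similar to 0.75 mg/kg.

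**The concern.** Two features of the rule matter.

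First, the interval describes one arm only. The limit it is compared with moves with the observed 0.75 mg/kg prevalence, which has sampling error of its own. The rule leaves that error out, so its false-pass rate is higher than a 95% interval suggests.

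Second, delta is an absolute number of points added to whatever the 0.75 mg/kg arm shows. If control carriage is well below 18%, or 0.75 mg/kg works less well than assumed, 6 or 7 points can equal or exceed the whole primaquine effect. A dose that adds nothing to DHA-PPQ could then pass. The trial has a concurrent control arm that would expose such a dose, but the rule does not use it.

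The trial looks for the lowest gametocytocidal dose, so a false finding of similarity is the error that damages its purpose most. The assumptions are not secure on the article's own account: the Background says 0.75 mg/kg has had a variable effect on transmission, and that African studies differ on what primaquine adds.

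**Working it through.** **Inputs.** From Sample size considerations: control 18%, 0.75 mg/kg 9%, 300 per arm, limits 15% and 16% (delta 6 and 7 points), 5% significance, 10% loss (300 × 0.9 = 270 evaluable). From Statistical analysis plan: the decision rule. Assumptions of this check: a Wilson interval, two-sided 5%, and the alternative prevalences in step 4.

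**Rule.** With x_L and x_R positives out of n in the lower-dose and 0.75 mg/kg arms and p = x_L/n, the dose passes if U(x_L) < x_R/n + delta, where U = [p + z²/2n + z√(p(1−p)/n + z²/4n²)] / (1 + z²/n) and z = 1.96. The chance of passing is the sum of the two binomial probabilities over all (x_L, x_R) that pass.

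**1. The plan's own figures.** Both arms at 9%, n = 300: 81.2% (6 points) and 90.0% (7 points). This matches the stated 80% and 90%, but only with 300 evaluable. At 270 the same rule gives 77.3% and 87.1%.

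**2. Error at the margin.** Take delta 6, true prevalences 15% and 9%, n = 270.
- Standard error, lower-dose arm: √(0.15 × 0.85/270) = 0.0217
- Standard error, 0.75 mg/kg arm: √(0.09 × 0.91/270) = 0.0174
- Standard error of the difference: √(0.0217² + 0.0174²) = 0.0278

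The rule allows 1.96 × 0.0217 = 0.0426, which is 0.0426/0.0278 = 1.53 standard errors of the difference, not 1.96. Exact enumeration gives a pass rate of 5.4%, and again 5.4% for delta 7 (16% versus 9%). A Wald interval for the difference gives 2.7% and 2.6%.

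**3. When the margin swallows the effect.** With a 50% reduction, the effect is half the control prevalence. Delta equals or exceeds it once control is 2 × 6 = 12% or lower, or 2 × 7 = 14% or lower.

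**4. Chance that a dose equal to control passes**, 270 per arm, the plan's rule:

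| Control and lower dose | 0.75 mg/kg | 6 points | 7 points |
|---|---|---|---|
| 18% (planned) | 9% (planned) | 0.45% | 1.1% |
| 12% | 6% | 4.7% | 9.8% |
| 12% | 8% | 19% | 31% |
| 8% | 4% | 21% | 36% |
| 18% | 14% | 18% | 27% |

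Changing to a difference interval alone does not cure this: at 8% versus 4% it still passes 18% or 33%. Requiring superiority to control at two-sided 5% brings the rows with control at 12% or 8% to 0.9–2.3%, and caps any such dose at about 2.5%.

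**5. Price for a truly equal dose** (9%, 9%, control 18%, 270 per arm):

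| Rule | 6 points | 7 points |
|---|---|---|
| Plan's rule | 77% | 87% |
| Difference interval | 69% | 81% |
| Difference interval and superiority to control | 65% | 75% |

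The superiority step alone has about 87% power.

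**The case against.** On the plan's own figures the rule is safe against a dose equal to control. The limit of 15% or 16% lies below 18%, and such a dose passes about 1% of the time or less. This stands. A reader might note that 6 or 7 points is 6/9 = 67% or 7/9 = 78% of the assumed effect, and infer that a useless dose could therefore be declared similar. That does not follow. The risk arises when an absolute margin meets lower carriage or a smaller effect than assumed. The article sets no fraction of the effect that must be preserved.

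The control arm is not ignored either. The first hypothesis covers any primaquine dose against DHA-PPQ alone. If each dose is tested, a dose equal to control fails about 97.5% of the time, and readers would see both results. This also stands. What is missing is the link: nothing says a dose must pass both.

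A reader might also infer that the choice between 15% and 16% is left until the data are seen. The documents do not support that. This is a journal article, the full analysis plan is not shown and may fix delta, those analysing the data are blinded, and power at two limits may be a sensitivity statement.

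Finally, the remedy costs power in a trial already recruiting. That is true, and the cost is given in full.

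**Conclusion.** The point holds for the decision rule as written. The single-arm interval roughly doubles the error at the margin, from 2.5% to about 5.4%, even if every planning assumption is right. The missing superiority condition has almost no effect at 18% and 9%. It matters if the assumptions fail, when a dose equal to control passes between 4.7% and 36% of the time in the 12%/6%, 12%/8% and 8%/4% scenarios. Those prevalences are assumptions, not forecasts. The figures also rest on 270 evaluable per arm, a Wilson interval and two-sided 5%.

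The point does not show that the margin by itself admits an ineffective dose, or that delta will be chosen after the fact. The two limits simply need to be reconciled to one.

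**What to change.** Declare a lower dose non-inferior only if both conditions hold at day 7:

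1. the upper limit of the 95% confidence interval for its difference in prevalence from the 0.75 mg/kg arm is below delta; and
2. that dose is itself superior to DHA-PPQ alone at the two-sided 5% level.

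State one delta, reconciling the 15% and 16% limits, before unblinding.

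No new data are needed, but there is a real cost in power. At 270 evaluable per arm, the chance of the claim for a truly equal dose falls from 87% to about 75% (7 points) or from 77% to about 65% (6 points). Restate the power on this basis. If the stated power is to be kept for the difference interval alone, n = (z_α + z_β)² × 2 × 0.09 × 0.91 / delta² gives:

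- 6 points, 80% power: (1.960 + 0.842)² × 0.1638 / 0.06², or 358 evaluable per arm
- 7 points, 90% power: (1.960 + 1.282)² × 0.1638 / 0.07², or 352 evaluable per arm

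Both are before loss. With recruitment under way since August 2013, the sponsor may prefer to accept the lower power and report it openly.
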